### Safety assessment

Adverse events and serious adverse events will be defined according to standard regulatory criteria. Site investigators and research coordinators will prospectively collect safety data through daily review of medical records and direct communication with treating clinicians. The severity, seriousness and causality of each event will be assessed by the local investigator. Prespecified adverse events that will be reported besides death within 28 days of randomisation in hospital are atrial arrhythmia, ventricular arrhythmia, mesenteric ischemia, myocardial ischemia, Takotsubo cardiomyopathy, renal failure requiring RRT, bilateral digital ischemia, cardiac arrest, ischemic stroke and haemorrhagic stroke (Table 4). Additional adverse events defined as potentially or causally related to the study intervention or are otherwise of concern in the judgement of treating clinician will also be recorded. In keeping with established practice of reporting serious adverse events in critical care trials, those events that are deemed part of the natural course of the primary illness or expected complications of the critical illness are not required to be reported [16, 17]. Serious adverse events meeting reporting criteria will be submitted to the coordinating centre within 24 h of site awareness and reported to the relevant human research ethics committees.

### Participant timeline

A schematic table (Table 1) showing the schedule of enrolment, intervention and assessment in accordance with the SPIRIT guidance [18] is presented. Relevant characteristics of screened patients including date of screening and reason for exclusion will be recorded. Patient flow will be presented as a CONSORT diagram (Fig. 1).

**Table 1 Tab1:** Schedule of enrolment, intervention and assessments

Activity	Screening	Baseline info	Day 0–5	Day 6–14	Day 28	Day 90
Eligibility criteria evaluation	x					
Informed consent	x					
Demographics	x	x				
Randomisation		x				
Past medical history		x				
Use of nephrotoxic agents		x	x	x		
Vasopressor dose/use		x	x			
Peak serum creatinine		x	x	x	x	
MAP (recorded 4 hourly)		x	x			
Intervention period			x			
Safety outcomes			x	x	x	
Renal replacement therapy			x	x	x	
MAKE-14			x	x		
Mortality			x	x	x	x

**Fig. 1 Fig1:**
[figure not shown]
CONSORT flow diagram

### Sample size

Based on our pilot feasibility study [11] and prospective cohort study [8], a sample size of 1260 is required to demonstrate an absolute risk reduction of 6% in the primary endpoint (14-day mortality) in the intervention arm, assuming a 20% incidence of 14-day mortality in the control arm, at an alpha level of 0.05 and power of 80% and allowing for 2.5% attrition. The absolute risk difference of 6% is a conservative estimate relative to the effect size observed in our feasibility study (14-day mortality rate of 13% versus 6% in the standard care versus individualised blood pressure target) [11] or the effect size observed in a pre-specified comparative analysis in our prospective cohort study (14-day mortality rate of 13% versus 22% (*p* = 0.04) in the group with lower-than-median blood pressure deficit versus the group with higher-than-median blood pressure deficit) [8].

### Recruitment

Participating ICUs will have the requisite research infrastructure at each site. We anticipate 30*–*35 ICUs to participate, and based on our previous experience, with a conservative enrolment average rate of 1–2 patients per site per month, the study enrolment would take another 3 years approximately to achieve its sample size. Eligible patients will be identified and screened by the local site research team in consultation with treating clinicians, based on daily review of ICU admissions. Informed consent will be obtained by trained investigators or research coordinators, either directly from patients or, when patients are unable to provide consent, from their legally authorised representatives. To support engagement and motivation across sites, the coordinating centre will conduct regular check-ins with the local research team to discuss site-specific issues and feedback. If recruitment falls behind schedule, contingency plans include additional site training and targeted feedback across participating centres.

### Blinding

Investigators responsible for day-to-day care cannot be blinded due to the nature of the intervention. Analyses will be performed by an independent statistician who will remain blinded to treatment allocation.

### Data collection

Data will be tabulated for patient characteristics (Table 2) and process of care measures (Table 3). This table will include demographic data (age, sex), Acute Physiology and Chronic Health Evaluation (APACHE) III risk score [19], type of shock, comorbidities (chronic hypertension, diabetes mellitus, chronic obstructive pulmonary disease, ischemic heart disease, congestive heart failure, chronic kidney disease, valvular heart disease and peripheral vascular disease), organ system diagnosis (sepsis, gastrointestinal, respiratory, cardiovascular, neurological, renal, haematological, metabolic, musculoskeletal/soft tissue and other), pre-illness blood pressure, period (in weeks) between last pre-illness blood pressure measurement and randomisation, need for mechanical ventilation, volume of intravenous fluid administered within the prior 24 h, fluid balance, exposure to nephrotoxic agents (intravenous contrast, aminoglycoside, vancomycin, non-steroidal anti-inflammatory drug, ACE inhibitor or angiotensin receptor blocker, gancyclovir, calcineurin inhibitor, or remdesivir) within the prior 72 h, pre-morbid creatinine level, MAP at or closest to randomisation, serum lactate and serum creatinine levels obtained at or just prior to time of randomisation, time from ICU admission to randomisation (in hours) and the time from initiation of vasopressor therapy to randomisation (in hours).

**Table 2 Tab2:** Baseline characteristics

Characteristics	Standard MAP (*n* = xxx)	Individualised MAP (*n* = xxx)
Age, median [IQR], years		
Males, *n* (%)		
APACHE III score, median [IQR]		
Co-morbidities, *n* (%)		
Chronic hypertension		
Diabetes mellitus		
Chronic obstructive pulmonary disease		
Ischemic heart disease		
Congestive heart failure		
Chronic kidney disease		
Valvular heart disease		
Peripheral vascular disease		
Diagnosis organ system, *n* (%)		
Gastrointestinal		
Respiratory		
Cardiovascular		
Sepsis		
Neurological		
Renal		
Metabolic		
Musculoskeletal or soft tissue		
Haematological		
Other		
Type of shock, *n* (%)		
Septic		
Cardiogenic		
Mixed		
Other		
Period between pre-illness blood pressure (BP) measurements and randomisation, median [IQR], weeks		
Number of pre-illness BP readings per patient, *n* (%)		
2		
3		
4		
5		
Pre-illness mean arterial pressure, median [IQR], mmHg		
Receiving invasive mechanical ventilation at randomisation, *n* (%)		
MAP at randomisation, median [IQR], mmHg		
Serum lactate at randomisation, median [IQR], mmol/l		
Pre-illness serum creatinine, median [IQR], micromole/l		
Serum creatinine at randomisation, median [IQR], micromole/l		
Intravenous fluid given within 24 h prior to randomisation, median [IQR], ml		
Fluid balance at randomisation, median [IQR], ml		
Exposure to nephrotoxic agents within 72 h prior to randomisation, *n* (%)		
ACE inhibitor or angiotensin receptor blocker		
Intravenous contrast		
Non-steroidal anti-inflammatory drug		
Aminoglycoside		
Vancomycin		
Calcineurin inhibitor		
Gancyclovir		
Remdesivir		
Number of nephrotoxic agents within 72 h prior to randomisation, median per patient [IQR]		
Time from ICU admission to randomisation, median [IQR], h		
Time from T0^§^ to randomisation, mean (SD), h		

*IQR* interquartile range, *APACHE* Acute Physiology and Chronic Health Evaluation, *BP* blood pressure,

*MAP* mean arterial pressure, *ACE* angiotensin converting enzyme

^§^ T0—Time-point, when vasopressor or inotrope support was initiated

**Table 3 Tab3:** Exposure variables and other process of care measures

Characteristics	Standard MAP (*n* = xxx)	Individualised MAP (*n* = xxx)
Target MAP on randomisation, median [IQR], mmHg		
MAP-deficit^*^ (time-weighted average), median [IQR], %		
Percentage of time spent with > 20% MAP-deficit^**χ**^, median [IQR], %		
Achieved MAP ^#^ during the treatment period, median [IQR], mmHg		
Time-weighted average vasopressor dose (noradrenaline-equivalent), median [IQR], mcg/kg/min		
Time from randomisation to cessation of vasopressors, median [IQR], h		
Exposure to nephrotoxic agents within 14 days after randomisation, *n* (%)		
ACE inhibitor or Angiotensin receptor blocker		
Intravenous contrast		
Non-steroidal anti-inflammatory drug		
Aminoglycoside		
Vancomycin		
Calcineurin inhibitor		
Gancyclovir		
Remdesivir		
Number of nephrotoxic agents within 14 days after randomisation, median per patient [IQR]		
Exposure to blood transfusion within 5 days after randomisation, *n* (%)		
ICU length of stay post randomisation among survivors, median [IQR], days		
Hospital length of stay post randomisation among survivors, median [IQR], days		

*IQR* interquartile range, *MAP* mean arterial pressure, mmHg

^*****^ MAP-deficit = [(pre-illness MAP − achieved MAP)/pre-illness MAP] × 100, using positive incremental area-under-the-curve of MAP-deficit during vasopressor therapy

^**χ**^ % Time spent with > 20% MAP-deficit = [Σ(time-periods with > 20% MAP-deficit)/total time with available MAP data] × 100

^#^ Achieved-MAP was derived as the time-weighted average of 4-hourly values over the active treatment period

The time when a vasopressor or an inotrope agent is initiated will be identified as T0. Punctual four hourly interval data on MAP and norepinephrine-equivalent vasopressor dose [12] will be monitored until a patient is weaned off vasopressor or inotropic support for at least 24 h or up to a maximum of 5 days, whichever is earlier (Fig. 2). The time-weighted average MAP-deficit, while on vasopressor or inotropic support, will be reported for all patients as a measure of “relative hypotensive load” as described previously [8]. Percentage MAP deficit will be defined as the difference between pre-illness MAP and achieved MAP, divided by pre-illness MAP, expressed as a percentage. A more detailed explanation is provided in the supplement. Pre-illness MAP will be derived as a mean of up to 5 most recent, discrete, pre-illness MAP observations during the 3 years prior to illness, ascertained from past health records. Daily fluid balance and exposure to blood transfusions will also be recorded. Further, exposure to nephrotoxic agents within 14 days of randomisation will be monitored. Safety events such as atrial arrhythmia, ventricular arrhythmia, mesenteric ischemia, myocardial ischemia, Takotsubo cardiomyopathy, bilateral digital ischemia, cardiac arrest, ischemic stroke and haemorrhagic stroke during the study period will be monitored for all patients. Indications to initiate RRT such as presence of metabolic acidosis (pH < 7.2), blood urea nitrogen level of more than 30 mmol/l, hyperkalaemia (K > 6 mmol/l), creatinine level of > 499 micromoles/l, anuria for more than 6 h, fluid overload or other reasons such as toxin removal or clinician’s preference to start early RRT will also be recorded.

**Fig. 2 Fig2:**
[figure not shown]
**a–c** Daily means and 95% confidence intervals for time-weighted average percentage MAP deficit, achieved MAP and noradrenaline-equivalent dose

### Data management

Data will be electronically entered at each participating site into a REDCap database hosted on Australian-based servers of Hunter Medical Research Institute. Individual access to REDCap database is restricted to study staff only via secure log in with multifactor authentication. Monitoring of the data collection and protocol adherence will be carried out at regular intervals. All the original and updated data-entry will be securely stored to retain an audit trail. At the end of study data collection, integrity checks will be performed to identify any conflicting data, which will be recorded and addressed with a consensus between two study investigators. After all queries are resolved, the database will be locked for final analysis and will be safely stored in a password-protected folder. The database will be securely backed up off site as per standard procedures for data security. Access to the final dataset will be limited to the study statisticians and members of the trial steering group.

## Statistical methods

Analyses will be carried out by a biostatistician using standard statistical software (SAS, Stata and/or R). All randomised patients will be included in an intention-to-treat analysis. Baseline characteristics (Table 2) and other process of care variables (Table 3) will be tabulated for both groups and reported as mean (± standard deviation or median (interquartile range) for continuous variables and as count (%) for categorical variables.

### Primary outcome

Effect estimates for 14-day all-cause mortality will be derived from multivariable logistic mixed effects models with a random intercept for site (assumed normally distributed on the logit scale, with a constant variance) to account for clustering within sites and fixed effects for treatment group, time between T0 (initiation of vasopressor therapy) and randomisation, APACHE III score at randomisation, noradrenaline-equivalent dose at randomisation and type of shock (Table 4). A two-sided *P*-value for the effect of treatment will be obtained from this model and values < 0.05 will be considered statistically significant. The effect estimates of interest will be the relative risk and risk difference (individualised care versus standard care). The relative risk estimate will be obtained as a ratio of the mean for each group of the individual predicted probabilities obtained from the logistic regression model. Differences of these means will be the risk difference. Bootstrapping, using 10,000 iterations, will be used to calculate 95% confidence intervals.

**Table 4 Tab4:** Outcome measures

	Standard MAP (*n* = xxx)	Individualised MAP (*n* = xxx)	Adjusted^*^ relative risk (95% CI)	Adjusted^*^ risk difference (95% CI)	*P* value
Day 14 all-cause mortality, *n* (%)					
Major Adverse Kidney Event^δ^ within 14 days of randomisation, *n* (%)					
- New requirement for RRT					
- Doubling of creatinine					
RRT- free days^#^ by day 28, *n* (%)					
Day 90 all-cause mortality, *n* (%)					

*RRT* renal replacement therapy

^*^ The model included random intercepts for sites and fixed effects for treatment group, the time between T0 (initiation of vasopressor therapy) and randomisation, APACHE III score at randomisation, vasopressor dose at randomisation and type of shock

^**δ**^ Major adverse kidney event (MAKE)−14 was a composite outcome of death, or new renal replacement therapy during the first 14 days, or doubling of serum creatinine from pre-illness level on day 14 or on day of discharge from ICU, whichever was earlier

^#^ Patients who died were assigned the worst score of − 1

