### Secondary outcomes

90-day all-cause mortality and MAKE-14: Analysis will be as described above for 14-day all-cause mortality.Time-to-event data will be displayed as Kaplan–Meier curves and log-rank tests will be used to test for significant differences between the two treatment groups (Fig. 3, Figure S6). For time to death, hazard ratios will be estimated with Cox proportional hazards regression, with a random effect for site and fixed effects for the exposure adjusted for the time between T0 (initiation of vasopressor therapy) and randomisation, vasopressor dose, APACHE III score at randomisation and type of shock.

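### Read literally, the formula for the primary relative risk and risk difference returns essentially the crude risks, although Table 4 labels them as adjusted

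*Protocol article*

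**What the plan says.** The Primary outcome section of the protocol article bases the effect estimates on "multivariable logistic mixed effects models with a random intercept for site" and "fixed effects for treatment group, time between T0 (initiation of vasopressor therapy) and randomisation, APACHE III score at randomisation", plus noradrenaline-equivalent dose and type of shock. The test of treatment comes from this model: "values < 0.05 will be considered statistically significant".

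The relative risk is then defined as a "ratio of the mean for each group of the individual predicted probabilities obtained from the logistic regression model". The next sentence reads: "Differences of these means will be the risk difference". Intervals follow: "Bootstrapping, using 10,000 iterations, will be used to calculate 95% confidence intervals".

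Table 4 heads the relative risk and risk difference columns as adjusted. Its footnote begins "The model included random intercepts for sites and fixed effects for treatment group" and lists the same covariates. The Secondary outcomes section carries the method over to 90-day mortality and MAKE-14: "Analysis will be as described above for 14-day all-cause mortality".

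The article does not say that each patient is predicted under both treatments, that the averages run over the whole trial population, or whether predictions include the site effect.

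**The concern.** The plain reading is to take each patient's fitted probability, average within each arm and compare the two averages. In a logistic model with a treatment term, that step undoes the covariate adjustment. The columns headed as adjusted would then not be adjusted for APACHE III, vasopressor dose, type of shock or time from vasopressor start to randomisation.

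A single row of Table 4 would combine a P-value from the adjusted model with an estimate and bootstrap interval that are in effect crude. The interval and the P-value could then fall on opposite sides of the significance boundary. These are the trial's headline figures. If the reading is settled only after the data are seen, the choice of primary estimate becomes post hoc.

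**Working it through.** **Scale.** No stated figure depends on this point, but the design inputs set the scale. For 20% versus 14%, two-sided 0.05 and 80% power:

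n per arm = [1.960·√(2·0.17·0.83) + 0.842·√(0.20·0.80 + 0.14·0.86)]² / 0.06² ≈ 614.1, rounded up to 615.

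The total is 1230, and 1230/0.975 = 1261.5, so 1262. The unpooled variant gives 612 per arm, 1224 in total and 1256 after attrition. The stated 1260 lies between the two and is not in question.

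**Algebra, ordinary logistic regression.** Maximum likelihood sets Σ xᵢⱼ(yᵢ − p̂ᵢ) = 0 for every model column j.
- Intercept column: Σ over all patients of (y − p̂) = 0.
- Treatment column: Σ over the individualised arm of (y − p̂) = 0.
- Subtracting: Σ over the standard arm of (y − p̂) = 0.

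The mean fitted probability in each arm therefore equals that arm's observed death proportion, whatever covariates are in the model.

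**Algebra, planned mixed model.** The corresponding equations hold with p̂ replaced by its average over the estimated distribution of the site effect given the data. Plugging in a single estimated site effect makes the identity near-exact. Setting the site effect to zero loosens it further.

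**Simulation.** 400 trials with N = 1260, 33 sites (the article expects 30–35) and 1:1 allocation within site. The model was a random-intercept logistic model fitted by maximum likelihood with 15-point Gauss–Hermite quadrature. The documents give no covariate effects, so these are assumptions: log-odds 0.9 per SD for APACHE III, 0.4 per SD for vasopressor dose, 0.1 per SD for time to randomisation, 0.4 for a binary shock type (20% prevalence), and a site SD of 0.4 on the logit scale. Average risks were 17.8% and 11.8%.

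| Estimator | Gap from crude RD, points: mean (max) | Gap from crude RR: mean (max) | Correlation of RD with chance APACHE imbalance |
|---|---|---|---|
| Crude | – | – | 0.22 |
| Arm means, ordinary logistic | 0 (2×10⁻¹⁰) | 0 (1×10⁻¹¹) | 0.22 |
| Arm means, mixed model, site effects included | 0.01 (0.06) | 0.003 (0.006) | 0.22 |
| Arm means, mixed model, site effect zero | 0.08 (0.38) | 0.007 (0.041) | 0.22 |
| Standardised over all patients, site effects included | 0.55 (2.0) | 0.026 (0.107) | −0.05 |

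All three arm-mean versions track chance APACHE imbalance as closely as the crude estimate does; standardisation nearly removes that dependence. The variance ratio of the risk difference, standardised to crude, was 0.924, so the crude variance is 1/0.924 = 1.08 times as large. The average gap of 0.55 points is about 9% of the 6-point design effect (0.55/6).

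In the simulated trial with the largest APACHE imbalance:
- crude: RD −11.0 points, RR 0.498;
- arm means with site effects: RD −11.05, RR 0.493;
- standardised: RD −9.3, RR 0.552.

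Further simulations (N = 1230, ordinary logistic, three assumed covariates, strongest log-odds 0.7 to 1.0 per SD) put the variance of the literal estimator about 5–14% above that of the standardised one.

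**Interval against P-value.** Under the same kind of assumptions, the crude interval and the adjusted P-value disagreed at 0.05 in about 7% of trials with an effect near the design target, using a Wald interval in place of the bootstrap. A second set of runs gave 5.9% and 8.5% near the target and 2.6% and 3.9% under the null. Standardising cut this to 0.3% or less.

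**The case against.** **The wording may be shorthand.** The sentence does not say that each group's own patients are averaged. A mean for each group can be condensed language for a mean under each treatment condition. The adjusted label, the covariate footnote and the use of a bootstrap, which two raw proportions would not need, all suggest that standardisation was intended. This stands. A reader might infer that the plan deliberately chose an unadjusted estimator; the documents do not show that.

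**The identity is not exact here.** A reader might infer that the formula simply returns the crude risks. That holds exactly only for ordinary logistic regression. The planned model has a random site intercept, and the article does not say how it enters the prediction. This stands, but none of the arm-mean versions restores covariate adjustment.

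**Validity is intact.** A reader might infer bias or a compromised primary test. Neither follows. Allocation is randomised 1:1, so the crude contrasts are valid, and significance is declared from the adjusted model's P-value under either reading. In 3,000 simulated null trials per scenario, the crude test rejected in 4.9% and 5.6% and the adjusted test in 4.7% and 5.7%. Site imbalance is also not a material part of the concern, because randomisation is stratified by site in blocks of 4 and 6.

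**A journal article condenses.** This carries little weight. The abstract and the Trial design section say that the analysis plan is published in this article. The text sends the reader to the supplement for MAP-deficit detail and the Bayesian analysis, not for this. The estimator is stated, and its plain reading conflicts with Table 4.

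**Conclusion.** The point holds as a defect in how the estimator is specified. On its plain reading, the formula yields estimates that are crude to reporting precision when site effects are in the prediction, and within about 0.4 points of the crude risk difference when the site effect is zero. That contradicts the adjusted label in Table 4 and separates the estimate and interval from the test.

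The cost is moderate: lost precision, no protection against chance imbalance in strong prognostic factors (an average shift of about 0.5 points and up to 2 points in simulation), and occasional disagreement between interval and P-value. The near-identity with the crude risks follows from the algebra. The size of the loss and the disagreement rates rest on assumed covariate effects, and the 7% figure also on a Wald interval in place of the planned bootstrap. The sample size is unaffected.

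**What to change.** Replace the two sentences that define the relative risk and risk difference with marginal standardisation:

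1. From the fitted model, predict every randomised patient's risk twice, once with treatment set to individualised and once set to standard, keeping that patient's covariates.
2. Average each set of predictions over all randomised patients, then take the ratio and the difference of the two averages.
3. State how the site random effect enters the prediction, for example by using the estimated site effects or by integrating over their distribution. In the simulation, using estimated site effects or zero moved the mean standardised risk difference only from −5.94 to −5.89 points, but the choice should be fixed in advance.
4. Repeat model fit, prediction and averaging in each bootstrap sample.
5. Apply the same text to 90-day mortality and MAKE-14.

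The cost is a few lines of plan wording and code. No change to data, design or sample size is needed, and recruitment is still under way.
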